## Abstract

**Background:**

Older adults who live in rural areas experience significant disparities in health status and access to mental health care. "Telepsychology," (also referred to as "telepsychiatry," or "telemental health") represents a potential strategy towards addressing this longstanding problem. Older adults may benefit from telepsychology due to its: (1) utility to address existing problematic access to care for rural residents; (2) capacity to reduce stigma associated with traditional mental health care; and (3) utility to overcome significant age-related problems in ambulation and transportation. Moreover, preliminary evidence indicates that telepsychiatry programs are often less expensive for patients, and reduce travel time, travel costs, and time off from work. Thus, telepsychology may provide a cost-efficient solution to access-to-care problems in rural areas.

**Methods:**

We describe an ongoing four-year prospective, randomized clinical trial comparing the effectiveness of an empirically supported treatment for major depressive disorder, Behavioral Activation, delivered either via in-home videoconferencing technology ("Telepsychology") or traditional face-to-face services ("Same-Room"). Our hypothesis is that in-homeTelepsychology service delivery will be equally effective as the traditional mode (Same-Room). Two-hundred twenty-four (224) male and female elderly participants will be administered protocol-driven individual Behavioral Activation therapy for depression over an 8-week period; and subjects will be followed for 12-months to ascertain longer-term effects of the treatment on three outcomes domains: (1) clinical outcomes (symptom severity, social functioning); (2) process variables (patient satisfaction, treatment credibility, attendance, adherence, dropout); and (3) economic outcomes (cost and resource use).

**Discussion:**

Results from the proposed study will provide important insight into whether telepsychology service delivery is as effective as the traditional mode of service delivery, defined in terms of clinical, process, and economic outcomes, for elderly patients with depression residing in rural areas without adequate access to mental health services.

**Trial registration:**

National Institutes of Health Clinical Trials Registry (ClinicalTrials.gov identifier# NCT00324701).

## Background

People who live in rural areas experience significant disparities in health status and access to care compared to their urban counterparts [1,2]. Access to appropriate mental health care services represents a significant problem in many rural and remote areas and as the ageing population expands, this problem will intensify over the next several decades without innovative solutions [1-4]. There is growing awareness that specifically tailored treatment and service delivery strategies are frequently needed for different populations of adult consumers of mental health services [3,5]. Access to appropriate mental health care services represents a significant problem in many rural and remote areas and this problem will intensify over the next several decades without innovative solutions [4]. In the mental health field, "telepsychology," (or "telepsychiatry" or "telemental health") represents a strategy for potentially addressing this longstanding access to care problem [6-8].

The strengths of telemental health include well-documented patient and provider satisfaction for a range of services [9-15]; strong support for the reliability of clinical assessments (eg, neuropsychological testing, clinical interviews, and mental status exams) relative to face-to-face assessments [16-20]; and evidence that medical patients would choose to receive it if it was available and would improve their access to care [21]. In addition, research has documented the effectiveness of telepsychiatry to treat specific mental health diagnoses such as depression [22-24] and anxiety disorders [25-27], as well as its effectiveness with specific populations including incarcerated patients [28,29], children and adolescents [30], rural populations [13,31,32] and older adults [16,33-35]. The weaknesses identified in the research literature include a paucity of rigorous cost and efficacy studies, particularly for specific populations, and lack of research into the legal, ethical and regulatory issues inherent in this application of technology to clinical practice [6,7,36].

The use of telemedicine to address urgent patient care needs for older adults has been identified as the first two of five priority areas for future development by the Department of Veterans Affairs (VA) [37]. Although there is widespread use of telepsychology to provide clinical services within and outside of the VA [38], there is insufficient research to determine if telepsychology service delivery is as acceptable or effective as traditional service delivery for older adults. In addition it remains unknown whether it is cost-effective for elderly veterans with depression residing in rural areas, without access to specialty geropsychiatric services. Thus, research that addresses the efficacy of this mode of service delivery is urgently needed.

This paper describes the rationale, study aims and objectives, and research design and methods of an ongoing four-year prospective, randomized clinical trial comparing the effectiveness of Behavioral Activation treatment for geriatric major depression delivered via in-home videoconferencing technology ("Telepsychology") compared to traditional face-to-face delivery ("Same-Room"), to test the hypothesis that in-home "Telepsychology" service delivery will be equally effective as the traditional mode (Same-Room).

### Rationale

The population of older adults is particularly well-suited for telepsychology for several reasons: (1) Over the next two decades there will be a large increase in the rural elderly population, and access to care is already a significant problem for many elderly adults with major depressive disorder (MDD) [3]; (2) telepsychology may be preferred by older adults, who avoid traditional mental health care due to embarrassment or stigma [39-43]; and (3) telepsychology may address significant age-related problems in ambulation and transportation [3,44]. Indeed, medically disabled older adults with ambulation difficulties, and those isolated older adults in rural areas, are among those at greatest risk of psychopathology, yet currently are the least likely to be able to obtain treatment [3]. Finally, results from a recent randomized trial also found telepsychiatry to be efficacious in the treatment of mild cognitive deficits among elderly persons [34].

### Study Aims & Objectives

The objective of the study is to test the hypothesis that in-home video-conferencing technology ("Telepsychology") will be as effective as the more traditional mode of service delivery ("Same-Room") for treating older adult veterans suffering from major depressive disorder (MDD). This objective will be accomplished by (1) Using an established, highly effective and well-tolerated behavioral treatment for depression (i.e. Behavioral Activation Treatment for Depression (BATD) [45-47]; (2) Employing a randomized between groups experimental design; (3) Examining standardized, repeated dependent measures of: (a) clinical outcomes, such as symptom severity, social functioning, and medical status; (b) process variables, such as patient satisfaction, treatment adherence, and treatment dropout rates; and (c) economic outcomes; and (4) conducting analyses to examine for outcome differences between African-American and Caucasian patients.

The primary research questions of the proposed study are:

1. Is in-home telepsychology for major depressive disorder in older adults as effective as same-room treatment on clinical and process outcomes?

2. Is in-home telepsychology for major depressive disorder in older adults cost-effective?

## Methods

The study is a 2 group randomized controlled trial with randomization of individual participants, blinded outcomes assessments at baseline, mid-treatment (4-weeks), post-treatment (8-weeks), 3-months, and 12-months, and concurrent economic evaluation.

### Location and Setting

The assessments and interventions will be conducted at the primary care and mental health clinics of the Ralph H. Johnson Veterans Affairs Medical Center (VAMC) located in downtown Charleston, South Carolina. The Ralph H. Johnson VAMC is a primary, secondary, and tertiary referral medical center providing acute medical, surgical, and psychiatry inpatient care as well as primary care and specialized outpatient services. Currently, there are 98 acute care beds and 28 nursing home care unit beds for a total of 126 operational beds. The primary service area extends from north of Myrtle Beach, SC, down to the surrounding counties of Savannah (Georgia, USA). For the most recent fiscal year (FY 2007), there were 41,645 unique patients, 4,000 discharges, 475,714 total outpatient visits, and 2,968 OEF/OIF enrollees and users. The Ralph H. Johnson VA Medical Center is a part of VA Southeast Network VISN 7 which includes facilities in Charleston, SC, Columbia, SC, Atlanta, GA, Augusta, GA, Dublin, GA, Birmingham, AL, Tuscaloosa, AL, and Central Alabama (Montgomery and Tuskegee campuses). The facility also has four Community Based Outpatient Clinics (CBOCs) in (1) Beaufort, SC – 53 miles to VAMC; (2) Goose Creek, SC – 17 miles to VAMC; (3) Myrtle Beach, SC – 83 miles to VAMC; and (4) Savannah, GA – 84 miles to VAMC.

### Ethics and Trial Registration

The study is funded by grant #IIR 04-421 from the Veterans Health Administration Health Services Research and Development program. The trial is approved by the joint Institutional Review Board (IRB) of the Ralph H. Johnson VAMC and the Medical University of South Carolina (HR#16402). The trial is registered on the United States National Institutes of Health Clinical Trials Registry (ClinicalTrials.gov identifier# NCT00324701), available online at: 

### Trial Population and Recruitment

Subjects will be 224 older male and female veterans (age 60 or older) presenting for services at VA primary care clinics and meeting DSM-IV [48] criteria for MDD. Actively psychotic or demented persons, individuals with both suicidal ideation and clear intent, and individuals meeting criteria for substance dependence will be excluded from participation; however, in order to maximize generalization of results, presence of other forms of psychopathology (eg, anxiety disorders) will not be a basis for exclusion. Participants who are incapable of giving informed consent due to mental incapacity or extreme distress will be excluded from the study. Because the inclusion of minorities in research on psychiatric disorders is important, about 40% of our sample will be African American, which is representative of the population of South Carolina.

We will use two complementary approaches to identify eligible study subjects. The first method will consist of systematic identification of patients with MDD. After obtaining IRB approval for a partial waiver of HIPAA, we will use clinic-billing records over the previous 12-month period to identify subjects with ICD-9 codes consistent with a diagnosis of MDD. The physicians of eligible patients will be notified of their patients' potential eligibility and asked permission to enroll their patients in this study. After consent is obtained from the physicians, letters of invitation on clinic letterhead signed by the patient's physician will be mailed to patients from the study clinics. The letter will provide information about the study, explain the study requirements, and clarify that only subjects that meet certain criteria will be eligible to participate in the study. The letter will include an addressed and stamped post-card that subjects can mail back to indicate interest or lack of interest in participating in the study. In addition, the letter will provide a telephone number that interested subjects can call to receive detailed information about the study. In the letter, subjects will also be informed that they will receive a follow-up call in two weeks unless they mail back the post card or call to decline being contacted. Subjects that mail back the post card and express interest or call the provided telephone number will receive detailed information about the study. Subjects who agree to participate will be asked to provide written consent and will be scheduled for the initial screening assessment.

The second method will consist of referrals from physicians, other clinic staff such as nurses, or patients themselves in response to recruitment flyers for the study. The Principal Investigator (PI) will share the goals of the study and inclusion/exclusion criteria with physicians and clinic staff during clinic administrative meetings. Physicians and clinic staff will be asked to refer appropriate subjects to the study research assistants. In addition, IRB approved recruitment flyers will be posted in prominent locations in the study clinics.

Regardless of recruitment pathway, research staff will obtain written informed consent, complete a screening for dementia and psychosis, and assure that participants meet DSM-IV [48] criteria for MDD. Those candidates meeting MDD criteria will then complete the remainder of the assessment battery (Tables 1 and 2).

**Table 1 T1:** Data Collection Schedule

Study Instrument	Screening Visit	Baseline Visit	4 Weeks Visit	8 Weeks Visit	3 Months Visit	12 Months Visit
**Screening/Baseline Assessment**						

Demographic Questionnaire	X					

Geriatric Depression Scale	X	X	X	X	X	X

SCID		X				X

Short Portable Mental Status Questionnaire	X					

						

**Multi-Method Assessment**						

Beck's Depression Inventory		X	X	X	X	X

Beck's Anxiety Inventory		X	X	X	X	X

SF-36		X	X	X	X	X

Medical Outcomes Study Social Support Form		X			X	X

Morisky Medication Adherence Form		X			X	X

						

**Process Variables**						

Charleston Psychiatric Satisfaction Scale			X	X	X	X

Treatment Credibility			X	X	X	X

Service Delivery Perceptions			X	X	X	X

Treatment Adherence (Therapists)			X	X	X	X

Session Attendance/Attrition (Therapists)			X	X	X	X

Prior Computer/Audiovisual Tech. Experience			X	X	X	X

						

**Resource Utilization**						

Baseline Visit Form		X				

Standard Follow-up Form					X	X

**Table 2 T2:** Study Instruments

**Geriatric Depression Scale** **(GDS) **[51]	The GDS is one of the most widely used measures of depression in the elderly population using the generally accepted cutoff score of 11. This 30-item measure shows good test-retest reliability and internal consistency. The GDS exhibits good concurrent validity, and excellent sensitivity, specificity, and positive predictive power in assessing depression with older adults.
**The Short Portable Mental Status Questionnaire **[85]	This is a ten item test that is quickly completed and will be used to screen for cognitive impairment (cutoff ≥ 7). The screen is effective in identifying cognitive impairment in a variety of geriatric populations.

**Structured Clinical Interview for DSM-IV** **(SCID-IV) **[50]	MDD and other psychopathology will be evaluated using this structured clinical interview based on the DSM-IV. The onset of the MDD will be specified. The SCID-IV has excellent interrater reliability on assessments of symptoms across a variety of disorders (overall kappa = 0.85).

**Beck Depression Inventory** **(BDI) **[52]	The BDI is a 21-item self-report scale, is among the most widely used instruments to measure depression. The BDI has high internal consistency (α = 0.86 – 0.91).

**Beck Anxiety Inventory** **(BAI) **[66]	The BAI is a 21-item self rating scale of anxiety symptomatology. Specific symptom clusters have been identified reflecting neurophysiological, subjective, panic, and autonomic dimensions. The BAI has good internal consistency and concurrent validity with the Hamilton Anxiety Rating Scale.

**Medical Outcome Study Short Form-36 Health Survey (SF-36) **[67]	The SF-36 is a 36-item questionnaire that measures health status and functioning over the past four weeks. The items vary from dichotomous (yes/no) responses, to ratings on a 6-point Likert scale. Responses are compiled into eight dimensions covering (a) Functional Status; (b) Well-Being; and (c) Overall Evaluation of Health. The SF-36 has good test-retest reliability as well as sensitivity to change in health status.

**Medical Outcomes Study (MOS) Social Support Survey **[86]	It measures four functional components of social support: 1) tangible support; 2) affection; 3) positive social interaction; and 4) emotional or informational support. The total scale (α = 0.97) and subscales (α = 0.91 to 0.96) have high internal consistency, good criterion and discriminant validity, and one-year test-retest reliability (0.72 to 0.76).

**The Morisky Adherence Score **[87]	This is a commonly used self-report tool to assess adherence to medications. It has good validity and reliability. This scale asks patients to respond "yes" or "no" to a set of 4 questions. A positive response to any question indicates a problem with adherence with a total possible score of 4; higher scores indicate poorer adherence.

**Charleston Psychiatric Outpatient Satisfaction Scale (CPOSS) **[53]	The CPOSS is 16-item measure, with a Likert scale response format, based on a general measure of patient satisfaction. In a sample of patients preliminary data showed the measure had excellent reliability (alpha = 0.96) and good convergent validity with relevant anchor items ("would you recommend this treatment to a friend or family member?").

**Treatment Credibility Questionnaire **[88]	To assess for differences in outcome expectancy, treatment credibility scales developed by Borkovec and Nau (1972) will be used. Four of the questions will be used for this study, with 10-point Likert scales. These include questions regarding how logical the treatment seems, how confident participants are about treatment, and their expectancy of success.

**Service Delivery Perceptions Questionnaire**	This questionnaire will be used to assess subjects' perceptions about variables specifically related to the mode of service delivery (e.g., the quality of communication, ease of use, willingness to use treatment).

**Prior Experience with Computer and Audiovisual Technology Questionnaire**	We will administer a short measure to learn more about participants' prior experiences and comfort level with computers and audiovisual technology.

**Resource Utilization Questionnaire **[89]	Previously validated questions on resource utilization will be administered as part of the baseline, 3-, and 12 month assessments. The questionnaires are 1 page long and capture information on hospitalizations, physician/professional visits, and medications. The baseline assessment will capture differences between groups and allow for the control of possible group variation during data analysis.

### Randomization

The study coordinator will verify all eligibility criteria prior to randomization. The procedure and risks will be explained to the patient and the consent form signed as per standard clinical practice. All subjects will be randomly assigned to one of two groups – Telepsychology (n = 112) and Same Room (n = 112). The randomization sequence will be generated by the senior biostatistician and provided in individual sealed envelopes to the data/statistical analyst who will be responsible for randomization. This information will remain confidential and not shared with the study sites in accordance with the CONSORT guidelines [49]. The study coordinator will call the data/statistical analyst to get subject randomization assignment. Once a randomization assignment is provided, the patient is entered into the study and will be included in the intention to treat analysis (Figure 1).

**Figure 1 F1:**
[figure not shown]
**Design and Study Flow**.

### Intervention and Control Groups

All subjects will receive the same individual mental health intervention for an 8-week period. Sessions will occur approximately once each week during this period, and each session will last for about 60 minutes. The intervention group (Telepsychology) will receive therapy via videophone while the control group (Same Room) will receive face-to-face therapy. All patients will receive 8 sessions of BATD. One of the strengths of the BATD protocol is that it is designed to be very straightforward, easily learned by therapists and patients, and can be implemented over an 8-session period. Initial sessions are used to build patient rapport and provide a rationale for activation-based treatment. Subsequent sessions are used to assess factors that might be maintaining depressed behavior (eg, determining if a deficit of reinforcing activities or a preponderance of punishing activities exists); assess functional aspects of the behavior itself (eg, is the depressed person receiving significant social reinforcement for being depressed); initiate efforts to increase the likelihood of engaging in reinforcing behaviors; and reduce the availability of unintended reinforcement for depressed behavior. Next, a systematic approach to behavioral activation is implemented. This is simply a process to increase the rate of enjoyable (ie, going to dinner with a friend) and functional (ie, grocery shopping) behaviors, with this increase resulting in a decrease in depression. Using a daily calendar, patients begin with a weekly self-monitoring exercise that serves as a baseline assessment of daily activities, and orients them to the quality and quantity of his or her activities on a daily basis. Following the introductory and assessment stages of BATD, emphasis in sessions two and three shifts towards the identification of goals within key life areas including relationships, employment, recreational activities, physical/health issues, and spirituality. From these goals, the individual will select specific behaviors that will help achieve these objectives. For example, the life area of family relationships may include the goal of rebuilding a relationship with a particular family member, which can be accomplished with specific behaviors such as calling the family member twice per week. To help facilitate engagement in the desired behaviors, each activity is placed within an activity hierarchy and rank-ordered from "easiest" to "most difficult" to accomplish. Patients then use a daily calendar to plan, *in advance*, the next week wherein they schedule a variety of activities, including both 'fun' (such as something they enjoy doing) or 'functional' (such as getting some undesirable chore out of the way so they do not have to worry about it any longer). The planning calendar serves as an activity log (in instances where patients do not follow the planned activity, they are instructed to update the calendar to reflect what they actually did). Behavioral Checkouts, or specific reviews of completed activities and concurrent moods are completed with therapists in session to monitor progress over the course of treatment as the patient graduates to different levels of the hierarchy of activities.

The therapist and patient collaboratively ensure that the behaviors that they are planning fit well within the life area and goals in that area as previously established. At the beginning of each session, the behavioral checkout occurs in which adherence to the planned calendar of activities is reviewed, and ensuing mood states are discussed. Specific behaviors and contextual parameters, including time of occurrence and duration of activity, are determined on the basis of the patient's level of success or difficulty with activities for the prior week. As an additional incentive for patients to complete the behaviors on the behavioral checkouts, patients are asked to identify and schedule weekly rewards, arranged to become available only after they have completed the planned activities a particular week. The treatment is flexible and we ensure that all activities (eg, pleasant activities lists) are age, gender, and culture appropriate.

Upon completion of the active treatment program described above, subjects from both conditions (Telepsychology, Same-Room) will be followed for 12 months. The outcome assessment battery will be administered to all subjects at the end of this follow-up period. Those who develop acute problems during follow-up will either be provided additional treatment by the project staff or will be referred to other appropriate treatment providers. In order to prevent distortions in the follow-up data, information on patients who receive further treatment will be analyzed separately.

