### Outcome Measures

#### Clinical Outcome Measures

The primary clinical outcome measure is the proportion (%) of patients who respond to treatment. Treatment Responder status will be determined using each of the dependent measures of depression (ie, Geriatric Depression Scale (GDS) [51]; Beck Depression Inventory (BDI) [52]; and SCID [50]. For the BDI and GDS, treatment responders will be those that demonstrate, at 12-month follow-up, improvement of at least 50% on the total score. For the SCID, treatment responders will be those who are no longer diagnosed with MDD. Dichotomous classifications for the GDS and the BDI will be achieved by defining treatment response as at least a 50% improvement from baseline to post-treatment level (percent change from baseline: [baseline-post]/baseline ≥ 50%). We will report analyses involving each measure of treatment response separately, but will take the a priori position that, in the case where results based on each of these analyses do not converge, overall conclusions regarding treatment response will be based on the two measures that concur. Thus, our indicator of treatment response will be in terms of each measure, as well as in terms of the converging data from at least two different measures.

The primary process outcome is score on the Charleston Psychiatric Outpatient Satisfaction Scale (CPOSS), [53] measured at the end of the 12-month follow-up period. The CPOSS is a 16-item measure with each item having a Likert-type format (total score is sum of the 16 items with range 16–80). Non-inferiority of patient satisfaction at the end of the 12-month follow-up period for the two modes of delivery will be evaluated via the one-sided non-inferiority 90% confidence interval approach to estimate the difference in end of study mean scores on the CPOSS for the Telepsychology and Same-Room conditions. The magnitude of the difference in satisfaction levels, as estimated by the confidence interval will provide useful clinical information and will allow a clinical judgment relative to the clinical non-inferiority of the of the two modes of delivery.

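### Analysing further-treated patients separately conflicts with intention to treat and can bias the 12-month comparisons, towards non-inferiority under the planning values

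*Protocol article*

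**What the plan says.** The rule is in the protocol article under Intervention and Control Groups. It first identifies the patients: "Those who develop acute problems during follow-up will either be provided additional treatment by the project staff or will be referred to other appropriate treatment". It then says: "In order to prevent distortions in the follow-up data, information on patients who receive further treatment will be analyzed separately". The same paragraph also states: "The outcome assessment battery will be administered to all subjects at the end of this follow-up period". The 12-month data on these patients should therefore exist.

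Under Randomization the article says: "Once a randomization assignment is provided, the patient is entered into the study and will be included in the intention to treat analysis".

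The outcomes measured at the end of follow-up are these:
- GDS and BDI response, in one of two definitions under Clinical Outcome Measures: "For the BDI and GDS, treatment responders will be those that demonstrate, at 12-month follow-up, improvement of at least 50% on the total score". The same paragraph, and Sample Size Determination and Power Analysis, also define response as the change from baseline to post-treatment.
- SCID response, meaning no remaining diagnosis of MDD. The SCID is scheduled only at baseline and 12 months.
- The primary process outcome, the CPOSS score, "measured at the end of the 12-month follow-up period".

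Under Data Analysis, missing data from patients who leave early count as non-response. Nothing there says how patients who were treated again, and who have 12-month data, are to be counted.

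**The concern.** Further treatment follows an acute problem that arises after randomisation. Whether a patient has such a problem may depend on how well the assigned delivery mode worked. Separating patients on that event means the remaining groups are no longer the randomised groups.

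The stated aim is to prevent distortion, but setting these patients aside can introduce it. If they are mainly treatment failures, removing them raises the observed response rate in both arms, and by more in the arm with more failures. At response rates near those planned, this narrows a true deficit for Telepsychology. In a non-inferiority trial with a margin of 0.15, a narrowed deficit makes a false claim of non-inferiority more likely.

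**Working it through.** **Inputs from the article** (Sample Size Determination and Power Analysis; Data Analysis): Same-Room response 0.70, margin 0.15, one-sided α = 0.10, power 0.85, 100 evaluable and 112 randomised per arm.

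**Reproducing the planned size.** n = 2 × 0.70 × 0.30 × (1.2816 + 1.0364)² / 0.15² = 100.3 per arm, in line with the stated 100. Power at n = 100 is 0.849. Allowing for 10% loss, 100 / 0.90 = 111.1, so 112.

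**Assumptions not in the article.** True response is 0.70 v 0.55, a deficit exactly at the margin. A share f of non-responders in each arm is treated further and set aside. No rate is given, so f runs from 0.1 to 0.5. The planning values belong to post-treatment GDS response; using them at 12 months is itself an assumption.

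**Formulas.** With true response p in an arm of 100:
- observed response = p / (1 − f(1 − p))
- analysed n = 100 × (1 − f(1 − p))
- P(declare non-inferiority) = Φ((0.15 − difference) / SE − 1.2816), with the unpooled SE

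**Example, f = 0.3.** Same-Room: 0.70 / 0.91 = 0.769, n = 91. Telepsychology: 0.55 / 0.865 = 0.636, n = 86.5. The difference is 0.133 and SE = √(0.769 × 0.231 / 91 + 0.636 × 0.364 / 86.5) = 0.068, which gives 0.150.

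| f | Same-Room | Telepsychology | Difference | False non-inferiority | Simulated (400,000 runs) |
|---|---|---|---|---|---|
| 0 | 0.700 | 0.550 | 0.150 | 0.100 | 0.104 |
| 0.1 | 0.722 | 0.576 | 0.146 | 0.111 | 0.111 |
| 0.2 | 0.745 | 0.604 | 0.140 | 0.127 | 0.128 |
| 0.3 | 0.769 | 0.636 | 0.133 | 0.150 | 0.150 |
| 0.5 | 0.824 | 0.710 | 0.114 | 0.231 | 0.234 |

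**Other removal patterns** (0.70 v 0.55 unless stated):
- More Telepsychology failures set aside (0.2 Same-Room, 0.4 Telepsychology): difference 0.074, rate 0.431.
- Responders set aside as often as failures (0.3 each): difference 0.150, rate 0.100, so no bias.
- Break-even when the Same-Room share of failures set aside is about 1.2 times the Telepsychology share (0.24 v 0.20). Beyond that the bias reverses: at 0.40 v 0.20 the difference is 0.191 and the rate 0.029.
- Lower response (0.40 v 0.25, f = 0.3): difference 0.165, rate 0.069, a reversal.

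**Keeping everyone at observed status.** If f = 0.3 and half of the further-treated failures become responders, Same-Room is 0.70 + 0.30 × 0.3 × 0.5 = 0.745 and Telepsychology is 0.55 + 0.45 × 0.3 × 0.5 = 0.6175. The difference is 0.1275 and the rate 0.174. Retention alone therefore does not settle how these patients should count.

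The figures are for a binary response. The effect on the CPOSS mean was not calculated.

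**The case against.** **The sentence does not say the patients are excluded.** It could describe an extra analysis beside the intention-to-treat one. It sits in the intervention section, and Data Analysis contains no such exclusion. This is the best defence, and it shows that the wording is ambiguous. But an extra analysis would not prevent distortion of the follow-up data, whereas setting the patients aside is meant to do so. No other section says that they stay in the main 12-month comparison. If an extra analysis was meant, the sentence still needs correcting.

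**The primary endpoint may not be touched.** This stands in part. Treatment given during follow-up cannot change response measured at the end of the 8-week course, and the sample size rests on that definition. The 12-month definition of GDS/BDI response, the SCID and the CPOSS remain exposed.

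**The direction is not fixed.** This stands. A reader might infer that the rule necessarily favours non-inferiority. The article does not support that: it speaks of acute problems rather than depressive relapse, and it admits patients with other psychopathology, so some further-treated patients may be GDS/BDI responders. The reversals above are possible.

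**Counting every further-treated patient as a non-responder is debatable.** This also stands. It could label someone a depression failure after treatment for a different problem. Using observed status in the assigned arm is a recognised alternative, though it can dilute a difference too.

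**Conclusion.** The concern holds as a conflict between the separate-analysis sentence and the intention-to-treat statement. Its consequence is a 12-month comparison conditioned on a post-randomisation event. At the planning values, with equal shares of failures set aside, the false non-inferiority rate rises from the planned 10% to between 11% and 23% for f from 0.1 to 0.5. The lower end is a small effect, and the article gives no basis for choosing within the range.

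Across all the patterns tried, the rate ran from about 3% to 43%. The planned error rate is therefore not assured, but a definite bias towards non-inferiority cannot be claimed. That direction requires three things: further-treated patients are mainly failures, Same-Room failures are not set aside appreciably more often than Telepsychology failures, and response is near 0.70.

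Confidence is high that the two statements conflict for the 12-month outcomes, and moderate on direction and size.

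**What to change.** Replace the sentence with text on four points:
1. All randomised patients stay in their assigned arm in every 12-month comparison, whether or not they received further treatment.
2. The primary analysis prespecifies how further-treated patients count for response, either as non-responders or by their observed 12-month status. The other choice is reported as a sensitivity analysis.
3. The proportion receiving further treatment is reported by arm.
4. The separate analysis of these patients is supportive description only.

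The time point that defines GDS/BDI response also needs to be reconciled, because it decides whether this rule reaches those endpoints.

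The cost is a few sentences in the protocol or analysis plan and one sensitivity analysis. No extra outcome assessment is needed, since the battery is already planned for all subjects at the end of follow-up. The change concerns analysis only and leaves the rule for giving further treatment as it is.
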